**9.2. Subjects’ confidentiality…………………………………………………………………………………..29**

**10. FUNDING AND INSURANCE……………………………………………………………………………………………29**

**11. AGREEMENT TO PUBLISH………………………………………………………………………………………………29**

**12. ATTACHMENTS……………………………………………………………………………………………………………..29**

**1. RATIONALE AND JUSTIFICATION OF THE STUDY**

The World Health Organization (WHO) regards the diagnosis and treatment of latent tuberculosis (TB) infection as an essential intervention to achieve the goal of the End TB Strategy by 2035 and the subsequent elimination by 2050 (1). Screening for and treatment of latent TB infection has become a priority as the pool of people at risk increases due to life expectancy improvement, along with chronic underlying diseases and immunosuppression conditions.

The end stage kidney disease (ESKD) increases by a factor of 6 to 25 the risk of TB, and the prevalence of TB among recipients of kidney transplant is 20- to 74-fold higher than in the general population (2). Available evidence, albeit scarce, supports systematic screening and treatment of these patients, and it is recommended by the guidelines (3, 4). The recommended treatment includes isoniazid (INH) for 6-9 months (6-9H), rifampicin (RMP) and INH combination for 3 months (3HR), or RMP alone for 4 months (4R).

The ESKD patients constitute a fragile population, with frequent intercurrent clinical events, polypharmacy, which often make latent TB difficult to treat, mainly because of adverse events. Data from the TB Unit of the Bellvitge University Hospital with 387 ESKD patients treated with 3HR, 6-9H or 4R prior kidney transplant, showed that 88% completed treatment satisfactorily, and adverse events were the commonest cause of permanent discontinuation (5). Central nervous system toxicity caused by INH is of particular concern in these patients (6-8). Seizures, encephalopathy, dizziness, and cerebellar syndrome have been reported. In our own experience, 9% of patients treated with regimens including INH presented dizziness, referred to as feeling “drunk”. In all the cases, it was invalidating, and improved in a few days after discontinuing treatment. Neurotoxicity has been related to the inhibition of the pyridoxin phosphorylation to the active metabolite, the pyridoxal 5-phosphate. In patients with ESKD, and particularly those under substitutive renal therapy, accumulation of INH metabolites along with the pyridoxal 5-phosphate removal by dialysis, lead to neurotoxicity. In addition, polymorphisms of the N-acetyltransferase (NAT)-2 *2, *5, *6, *7 and *14 alleles, which confer the slow- acetylator phenotype, would contribute to increasing levels of INH and its metabolites, and risk of neurotoxicity (9).

The short-course rifampicin-containing regimens, with or without INH, are currently recommended as the first line treatment for latent TB infection. The combination of weekly rifapentine (RPT) and INH, under supervised administration for 3 months (3HP), has been shown to be no-inferior to the 9H regimen (10), and has already been approved for the first-line treatment of latent TB infection in the USA (11). A metanalysis showed that 87.5% of subjects treated with the 3HP regimen completed treatment, as compared with 65.9% of those treated with INH- or RMP-containing regimens (12). However, the available evidence in ESKD patients is limited to a small number of cases reported in the literature (13-15). A retrospective study with 153 candidates to kidney transplant with latent TB, 93% of the 43 3HP-treated patients and 47% among the 110 treated with the INH for 9 months completed treatment (13). In another two studies, including 17 and 12 transplant candidates treated with 3HP, completion rates were 76% and 100% respectively (14, 15).

The unanimity of the guidelines about the systematic treatment of latent TB in patients with ESKD contrasts to the limited evidence on safety, tolerability, and completion rates of treatment in this population. Among other reasons, ESKD patients and candidates to kidney transplant have been systematically excluded from clinical trials evaluating latent TB treatment. Clearly, knowledge on which treatment regimens are better tolerated and more convenient for latent TB in ESKD patients is urgently needed. Precise guidance on posology and administration (dose adjustment, pre- or post-dialysis administration), toxicity (toxicity profile, how to prevent it and how to monitor it), and graded alternatives are currently lacking. In line with our previous research on the optimization of diagnosis and treatment of latent TB, we aimed at assessing treatment completion of 3 short-course regimens (3HR, 4R and 3HP) for treatment of latent TB in ESKD patients. For this purpose, and based on our pre-transplant program’s data at the TB Unit of the Bellvitge University Hospital, we will compare 4R and 3HP regimens with the 3HR (control) regimen.

We will work with the hypothesis that the 3HP and 4R regimens will be better tolerated than the 3HR regimen, which will result in a better treatment completion. After an exhaustive review of the literature and the Clinical Trials Registry (https://www.clinicaltrials.gov/), we did not find any study in the field, published or registered.

**2. OBJECTIVES AND PURPOSE OF THE TRIAL**

- **Primary objective**

To determine if treatment completion with either three months of once-weekly isoniazid plus rifapentine (3HP) or four months of daily rifampicin (4R) or both is better in comparison to three months of daily isoniazid plus rifampicin (3HR) for treatment of latent TB infection in patients with end-stage kidney disease.

- **Secondary objective**

To determine the safety and tolerability of a 3HR, 3HP, and 4R regimens for the treatment of latent TB infection in patients with end-stage kidney disease.

**3. TRIAL DESIGN**

**3.1. Statement of the endpoints**

- **Primary endpoint**

The primary endpoint will be the proportion of participants who complete the assigned treatment regimen, defined as: 1) 90 doses within a maximum of 16 weeks, without interruptions longer than 2 weeks, and no more than on 2 occasions, for the 3HR arm (control); 2) 12 doses within a maximum of 14 weeks, without interruptions longer than 10 days, for the 3HP arm (experimental 1), and 3) 120 doses within a maximum of 20 weeks, without interruptions longer than 2 weeks, and no more than on two occasions, for the 4R arm (experimental 2).

- **Secondary endpoints**
- Proportion of participants who definitively discontinue the assigned treatment because of adverse events, regardless of its relationship to the treatment of the study.
- Proportion of participants who definitively discontinue the assigned treatment because of adverse events related to the treatment of the study.
- Crude mortality: Number of participants who die while on the study, regardless of its relationship to investigational medicinal products (IMPs) of the study.

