**4.3. Participant withdrawal criteria**

Each participant has the right to withdraw study at any time. In addition, the investigator may discontinue a participant from the study at any time if they consider it necessary for any reason including:

- An adverse event that requires discontinuation of the study medication, mainly liver toxicity caused by isoniazid or rifamycins.
- Non-attendance at two consecutive visits, if it was not because of death.
- Not completing the assigned treatment, for any reason, within the scheduled frame-time (1. not completion of 90 doses within a maximum of 16 weeks, without interruptions longer than 2 weeks, and no more than on 2 occasions, for the 3HR arm [control]; 2. not completing 12 doses within a maximum of 14 weeks, without interruptions longer than 10 days, for the 3HP arm [experimental 1] , and 3. Not completion of 120 doses within a maximum of 20 weeks, without interruptions longer than 2 weeks, and no more than on two occasions, for the 4R arm [experimental arm 2]).

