**4.4. Follow-up of participants withdrawn from the trial**

Participants withdrawn from the study because of adverse events will be followed up for four weeks beyond the withdrawal.

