A blood sample will be obtained in a subset of 100 participants at the coordinator site (Bellvitge University Hospital), for a sub-study on polymorphisms of the N-acetyltransferase (NAT)-2, to determine the acetylator profile (slow/rapid).

- **Allocation visit.** It will be the day 0 visit. Once the written informed consent has been signed, the investigator will proceed to randomize the participant.
- **On-treatment visits.** Participants will undergo follow-up visits while on treatment at days 15, 30, 60 and 90 for the 3HR (control) and the 3HP (experimental 1) arms, and 15, 30, 60, 90 and 120 for the 4R (experimental 2) arm. Adverse events, concomitant medication, and adherence will be assessed by means of a clinical interview at each visit, and blood tests at days 30, 60 and 90 for 3HR (control) and 3HP (experimental 1) arms, or 15, 60 and 120 for the 4R (experimental 2) arm.
- **Close-out visit.** In all the three arms, participants will be assessed 4 weeks after finishing the assigned treatment, at day 120 for the 3HR (control) and 3HP (experimental 1) arms, and day 150 for the 4R (experimental 2) arm.

Visits will be face-to-face at days 30, 60 and 90 for 3HR (control) and 3HP (experimental 1) arms, or 30, 60 and 120 for the 4R (experimental 2) arm. For the 4R arm, the visit at day 90 will be also performed by a phone call. Fifteen-day and post-treatment visits will be done by means of video- or telephone-call, whenever the investigator deems it is safe, and the participant agrees.

- **Monitoring treatment compliance**

Compliance with treatment will be monitored by clinical interview, counting leftover tablets. Assessment of urine colour (orange colour caused by rifampicin) will be carried out on participants with residual diuresis at each face-to-face visit.

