**5.4. Discontinuation of study drugs due to adverse events**

Certain events or conditions may necessitate temporary discontinuation of the study medications. Patients who experience such events or conditions, however, will still be "on study" and will be followed until study completion. Any patient for whom the study medication is temporarily discontinued will be restarted on study medication as soon as possible. If study drugs are definitively discontinued, alternative therapy for latent TB may be administered at the investigator's discretion.

- **Temporary Discontinuation**

Criteria for temporary discontinuation of the study medication:

- Development of a toxicity that, depending on its nature and severity, requires discontinuation of the study medication until the toxicity resolves as indicated in the preceding toxicity management section.
- Development of another medical condition that makes the administration of the study drug inadvisable. The decision to temporarily discontinue the study medication in this situation will be at the investigator's discretion. The period during which the patient is off study medication will be as short as clinically possible.
- **Definitive Discontinuation**

Criteria for definitive discontinuation of study therapy:

- Development of a toxicity that warrants definitive discontinuation of any study medications.
- The patient refuses further study therapy. If a patient refuses further study medication, they will be treated with a non-study regimen, and there will only be a post-treatment visit, four weeks after discontinuing the treatment.
- In the investigator's judgment, continuation of the medication is no longer in the best interest of the patient.
- Liver toxicity: ALT and/or AST elevation >5-fold of the upper limit of the normality or clinical hepatitis during treatment for latent TB infection with one of the IMPs.
- Neurotoxicity: Encephalopathy, dizziness, or cerebellar syndrome during treatment with INH-including regimens. It is commonly referred to as feeling “drunk”. It is usually invalidating and improved after discontinuing treatment.

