**7. ASSESSMENT OF SAFETY**

**7.1. Monitoring, recording, and reporting of adverse events**

**Adverse event (AE)** is any noxious, unintended, or untoward medical occurrence that may appear or worsen in a subject during the study. It may be a new intercurrent illness, a worsening concomitant illness, an injury, or any concomitant impairment of the subject’s health, including laboratory test values, regardless of aetiology. Any worsening (i.e., any clinically significant adverse change in the frequency or intensity of a pre-existing condition) should be considered an AE.

Any sequel of an accidental or intentional overdose of an investigational product should be reported as an AE or serious adverse event (SAE). In the event of overdose, the subject should be monitored as appropriate and should receive supportive measures as necessary. All subjects will be monitored for AEs during the study.

**All AEs** will be recorded by the investigator from the date the subject gives the written consent to four weeks after finishing the assigned treatment, as well as those serious adverse events made known to the Investigator at any time thereafter that are suspected of being related to one of the Investigational Medical Products (IMPs).

**All AEs** and **SAEs** will be recorded on the AE page of the CRF and in the subject’s source documents.

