**8. STATISTICAL METHODS**

**8.1. Statistical analysis**

The efficacy analysis will be performed on the modified intention-to-treat population, which will consist of all randomized subjects. The proportions of participants who completed the assigned treatment in the 3HR arm (control) will be compared with the proportions in either 3HP arm (experimental 1) or 4R arm (experimental 2). Since renal replacement therapy could have a potential influence on medication tolerance, especially INH, and thus could influence outcome, the analysis for the primary endpoint will be performed for the population as a whole and by subgroups (non-dialysis, on haemodialysis, or on peritoneal dialysis).

For safety, analyses will be performed on all randomized subjects who have received at least one dose of the assigned study treatment. Likewise, proportions of permanent discontinuation of the assigned treatment, related and unrelated to the study medication, and death, in the control arm will be compared with either experimental arm.

Statistical analyses will be performed by two investigators of the Biostatistics Unit of the IDIBELL, who will remain unaware of the trial-group assignments until the analyses have been completed. Differences between arms will be tested by Student’s t-test, if normally distributed, or a Wilcoxon two-sample test, if not normally distributed, or by chi-square analysis for categorical variables. Whenever possible, estimators will be given 95%CI. Statistical significance was set at a p-value <0.025. Treatment of the data and analysis will be performed with the statistical package R, version 3.4.1 or superior.

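### Deaths are counted over a planned 150 days in the 4R arm but 120 days in the control arm, and compared as simple proportions with no common horizon

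*Protocol*

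**What the plan says.** Protocol section 3.1 lists crude mortality as a secondary endpoint: the "Number of participants who die while on the study", whatever the relation to the study drugs. It gives no time point.

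Time on study follows from the visit schedule. Section 5.1 places the close-out visit "at day 120 for the 3HR (control) and 3HP (experimental 1) arms, and day 150 for the 4R (experimental 2) arm".

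Several provisions govern people who stop early:
- Section 4.4: "Participants withdrawn from the study because of adverse events will be followed up for four weeks beyond the withdrawal".
- Section 5.4, for those who refuse further therapy: "there will only be a post-treatment visit, four weeks after discontinuing the treatment".
- Section 4.3 gives other grounds on which the investigator may withdraw someone, such as "Non-attendance at two consecutive visits, if it was not because of death". No later follow-up is stated for these.

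Section 7.1 records adverse events "from the date the subject gives the written consent to four weeks after finishing the assigned treatment". After that, only serious events suspected to be related to a study drug are captured.

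Section 8.1 says that the proportions for permanent discontinuation "and death, in the control arm will be compared with either experimental arm", and that differences are tested "by chi-square analysis for categorical variables".

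**The concern.** A proportion dying depends on how long people are watched. Here the planned window is set by the length of the regimen, so the 4R arm has 30 more days in which a death can be counted than the control arm. With no difference in risk, 4R is still expected to show more deaths. A chi-square test on the proportions cannot separate that from a drug effect.

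Early stopping is a second source of unequal observation, and it can affect both planned contrasts. Someone withdrawn for an adverse event, or who refuses therapy, has about four weeks of further observation. For other withdrawals the protocol states none. The arm with more early stops may therefore have fewer of its deaths counted. The trial's hypothesis in section 1 is that 3HR is the least well tolerated regimen. If so, control deaths would be undercounted for this reason too, adding to the apparent excess on 4R.

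At stake is the reading of a named safety endpoint in a frail population in which some deaths unrelated to treatment can be expected.

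**Working it through.** **Inputs from the protocol.** Close-out is day 120 (3HR, 3HP) or day 150 (4R), section 5.1. There are 75 participants per arm, section 8.2. The significance level is 0.025 with sidedness not stated, section 8.1; it is taken as two-sided here.

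**Assumed input.** Annual mortality m, which the protocol does not give, is varied from 5% to 20%. The hazard is constant and equal in all arms.

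**Step 1: the stated close-out days.** Treatment length plus 28 days gives 90 + 28 = 118 (stated 120) and 120 + 28 = 148 (stated 150). Both agree within two days, so the stated days are reasonable nominal visit days.

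**Step 2: follow-up ratio.** 4R versus 3HR: 150 / 120 = 1.25. 3HP versus 3HR: 120 / 120 = 1.00.

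**Step 3: expected deaths under equal hazards.** Daily hazard h = −ln(1 − m) / 365.25. Risk to day t = 1 − exp(−h·t). Expected deaths = 75 × risk. For m = 10%, h = 0.10536 / 365.25 = 0.000288. The risk is then 3.40% at day 120 and 4.23% at day 150.

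| Assumed annual mortality | Risk to day 120 | Risk to day 150 | Ratio | Expected deaths per 75, day 120 | Expected deaths per 75, day 150 | Excess (from unrounded values) |
|---|---|---|---|---|---|---|
| 5% | 1.67% | 2.08% | 1.25 | 1.25 | 1.56 | 0.31 |
| 10% | 3.40% | 4.23% | 1.24 | 2.55 | 3.18 | 0.62 |
| 15% | 5.20% | 6.46% | 1.24 | 3.90 | 4.84 | 0.94 |
| 20% | 7.07% | 8.76% | 1.24 | 5.30 | 6.57 | 1.27 |

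**Step 4: chance of a false finding against 4R.** This is the exact binomial enumeration of the uncorrected chi-square test with 75 per arm, counting only rejections in which 4R has more deaths. At 10% annual mortality the probability is 0.009 with equal follow-up and 0.019 with 120 versus 150 days. At 20% it is 0.011 and 0.029.

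**Step 5: early stops.** As an illustration, a participant withdrawn at day 30 for an adverse event is followed to about day 30 + 28 = 58. That is 58 / 120 = 48% of the planned time of a 3HR or 3HP completer. The total effect on an arm cannot be computed, because the protocol gives no rate or timing of early stops by arm.

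**Step 6: does another section equalise follow-up?** Section 5.4 keeps people on study until completion, but for temporary discontinuation only. Section 7.11 mentions at least six months of follow-up before the safety board meets, but section 5.1 lists no visit after close-out. Neither supplies a common horizon.

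**The case against.** The strongest reply is that the effect is too small to matter. Crude mortality is the last-listed secondary endpoint, the trial was not sized for it, and an excess of 0.3 to 1.3 expected deaths will usually be lost in chance variation. That largely stands. With the risks above and 75 per arm, the probability that 4R actually shows more deaths than 3HR is 0.45 at 5% annual mortality, 0.52 at 10% and 0.59 at 20%. A reader might infer that 4R is bound to look worse; the figures do not support that. What remains is a bias of known direction that costs little to remove.

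A second reply is that following every regimen for the same period after its last dose is a sensible safety design, and that time at risk can be handled in the statistical analysis plan. The first half is fair for adverse events. The second half is only partly right: an analysis plan can choose a method, but it cannot recover unrelated deaths after the recording window that nobody was asked to collect.

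Some stronger readings are tempting but not supported:
- *Both contrasts are biased by design.* 3HP and 3HR share the day-120 close-out, so the 30-day gap does not affect that comparison.
- *Withdrawal for non-completion cuts observation to four weeks.* The four-week limit is stated only for adverse-event withdrawals and refusal of therapy. Completion is judged at the end of the maximum window (section 6.2: week 16, 14 or 20), so a withdrawal decided then would hardly shorten observation.
- *The close-out days contradict the four-week rule.* A late finisher would reach four weeks after the nominal day (for 3HR, 16 × 7 + 28 = day 140; for 4R, 20 × 7 + 28 = day 168). The stated days are nominal and match on-time completion. Even on the late-finisher dates 4R is watched longer, at 168 / 140 = 1.20.

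**Conclusion.** The point holds for 4R versus 3HR as a built-in difference in planned follow-up. The expected death ratio is about 1.24 under equal hazards, or roughly 0.3 to 1.3 extra expected deaths per 75 participants. The ratio hardly depends on the assumed mortality; the number of deaths does, and it rests on the assumed 5% to 20% a year, a constant hazard and follow-up to the nominal close-out days.

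For 3HP versus 3HR there is no planned imbalance. Bias there can come only from early stops. It could go either way and cannot be sized from the protocol.

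This is a change worth making before the data are collected, not a threat to the trial's primary conclusion.

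**What to change.** Redefine the endpoint in section 3.1 as death from any cause between randomisation and one common day in all three arms. That day should be no earlier than the 4R close-out at day 150. Count deaths to that day whether or not the participant stopped treatment or was withdrawn, unless consent to follow-up is withdrawn. Add to sections 4.4 and 5.1 a vital-status check by phone or record review at that day, and state in section 8.1 that arms are compared at that horizon. At the planned follow-up, the ratio then becomes 150 / 150 = 1.00.

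Shortening every arm to day 120 is not a good substitute. It would drop the post-treatment period for 4R and, for those using the permitted 20 weeks (day 140), some deaths on treatment.

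The cost is the change of wording plus one vital-status check for each 3HR, 3HP or withdrawn participant. No additional face-to-face visit is needed.

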**3.2. Trial type**

Prospective, open-label, randomized (1:1:1), superiority, multicentre clinical trial with parallel group design, comparing three short-course rifamycin-based regimens for the treatment of latent TB infection in patients with end-stage kidney disease.

